### Ethics

2.22

The research protocol complies with the Declaration of Helsinki. The ethics approval letter and consent letter of the research protocol came from the ethics committee of Nanping first hospital (approval number: NPSY202005001). The research background and main objectives, as well as potential benefits and risks, will be fully explained to participants and their families. Before participating in the study, participants will sign an informed consent form.

### Dissemination

2.23

The research protocol has been registered and can be used on the website of the Chinese Clinical Trial Registration Center (http://www.chictr.org.cn/, with the identifier ChiCTR2000033908). The research results will first be communicated to each participant, and then disseminated to researchers, healthcare providers, healthcare professionals, and the public through courses, presentations, and the Internet, regardless of the degree or direction of its impact. The results will also be recorded in a peer-reviewed academic journal in the publication.

## Discussion

3

In our study, after 24 weeks of training on Baduanjin and 4 weeks of follow-up. To observe the effect of Baduanjin on the main symptoms of chronic low back pain from the perspective of pain and dysfunction. In terms of quality of life, degree of disability and overall perception, to verify the impact of Baduanjin on patients’ daily life quality. Our research also provides safety assessment and economic benefit analysis. Baduanjin is a traditional Chinese exercise method. In recent years, more and more studies have used Baduanjin to assist the treatment of chronic obstructive pneumonia, coronary heart disease, hypertension and other diseases, as well as the rehabilitation of spinal joint diseases.^[38–42]^ Some previous studies have also confirmed the beneficial effects of Baduanjin on CLBP in terms of symptoms and activities.^[23]^ Some opinions believe that Baduanjin mainly uses the spine and waist as the axis to exercise, which is conducive to improving waist activity, improving waist muscle strength, and enhancing waist metabolism.^[43]^ Baduanjin requires patients to adjust their breathing and enter meditation.^[25]^ The state is conducive to the relaxation of tense muscles and the relief of pain. Nevertheless, the current design of the safety and effectiveness of Baduanjin in the treatment of chronic low back pain is still lacking. Therefore, this study will provide evidence on the usefulness of Baduanjin to the patient population.

Our research has many advantages. First of all, All Baduanjin are personally guided by professional teachers of more than 5 years to improve the quality of experimental data. Second, we will not only assess pain intensity, but also clinical relevance, quality of life, level of disability, and overall assessment. Third, the intervention effect of each recorded time point was analyzed statistically, build a hybrid linear model, to provide basic data for the treatment course and training frequency of Baduanjin. Fourth, economic evaluation is included for the first time to provide data for the urban benefit of Baduanjin. Fifth, safety index evaluation is included for the first time to verify the safety of Baduanjin training. However, our research also has some limitations. First of all, our sample size calculation may be overestimated. According to previous study, the duration of treatment was only 8 weeks, while ours was 24 weeks. Secondly, the control group used in the study is different from ours, which may affect the results of the study. Finally, the daily activity of the patients in the control group could not be quantified. After the inclusion of the patients, we could only see those with significantly increased or decreased daily activity, and carried out elimination management, but we could not make quantitative comparison with the patients in the intervention group.

Despite its limitations, the results of this trial are expected to provide evidence for the efficacy, safety and economic benefits of Baduanjin in the treatment of chronic low back pain. To provide medical staff, medical staff and patients with long-term exercise therapy plan recommendations.

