### Research design

2.2

This study is a randomized, controlled clinical trials, will conform to the conditions of 90 participants according to the proportion of 1:1 were randomly divided into intervention group (Baduanjin group) and control group (not exercise training group). All the members of the intervention group received Baduanjin training 3 times a week for 24 weeks. All cases in the control group did not receive any exercise training for 24 weeks. Primary and secondary outcomes will be measured at baseline, 8, 16 and 24 weeks after intervention, and the next 4 weeks. The research design flowchart is shown (Fig. 1). The research protocol was described in accordance with “ SPIRIT 2013 statement: defining standard protocol items for clinical trials ”.^[29]^

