### Sample size calculation

2.7

Perform sample size calculations to determine the appropriate number of participants. The main outcome will be the change of VAS score between the intervention group and the control group from before the intervention to the end of the last intervention. As far as we know, a previous clinical trial evaluated the effects of Baduanjin and conventional rehabilitation intervention for 8 weeks.^[28]^ The change of VAS score after treatment group (8^th^ week) was 2.37 ± 1.7 in the treatment group and 3.70 ± 1.39 in the control group. The following indicators will be considered: α = 0.05, statistical power of 95%, and follow-up loss of up to 20%. We use G∗POWER 3.1.9.7 (http://stats.idre.ucla.edu/other/gpower/) to calculate that the sample size of this study is 45 patients per group. Therefore, a total of 90 participants are required.

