### Statistics

2.21

All data are statistically analyzed using Statistical Product and Service Solutions (SPSS©), version 20.0 (IBM Corp., Armonk, NY, USA). Continuous variables will be mapped by the mean and its SE (normal distribution) or median and IQR (non-normal distribution). Categorical variables will be delineated as a frequency or percentage. The baseline characteristics between the comparison groups will be compared using the *t* -test or Mann-Whitney *U* test for continuous variables, while Pearson χ^2^ or Fisher exact test will be employed to compare categorical variables. The analysis of primary or secondary results will be established with the intent to treat principle, and missing data will be interpolated using multiple imputation methods. Student's *t* test or Mann-Whitney *U* test will be used to analyze the difference between the intervention group and the control group at each time period (8 weeks after the intervention, 16 weeks, and 24 weeks or 4 weeks of follow-up). In the safety analysis, the total adverse event rate and adverse event rate associated with Baduanjin were tested by Pearson χ^2^ or Fisher's exact test.

Primary analysis: treatment efficacy. The statistical analysis of primary and secondary results will be based on treatment principles. The effect of the intervention on pain distress, pain intensity, function, disability, and overall sensory effects will be determined using a linear mixed model (random intercept and fixed coefficient), which includes treatment, time, and time interaction. The treatment coefficient of time interaction provides an estimate of the effect of Baduanjin intervention. The magnitude of the treatment effect will be calculated for each follow-up time point. If there is a statistically significant treatment effect at any point in time, we will also calculate the number of treatments (NNT) required to achieve pain recovery.

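### The Discussion says the trial will verify the safety of Baduanjin, but a difference test of adverse event rates in 45 v 45 patients cannot support that claim

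*Protocol article*

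**What the plan says.** Section 2.1 (Objectives) lists safety outcomes within the main objective. The Discussion gives as the fifth strength of the study that "safety index evaluation is included for the first time to verify the safety of Baduanjin training", and its closing paragraph expects the trial to supply evidence on safety as well as efficacy and cost.

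Two places say how safety will be handled. Section 2.18 (Assess safety) plans to record every adverse event, to do vital signs, blood tests and neurological checks, and to calculate adverse event incidence. Section 2.21 (Statistics) adds the inference: "In the safety analysis, the total adverse event rate", and the rate of events attributed to Baduanjin, are compared by Pearson chi-squared or Fisher's exact test. No margin or precision target is given.

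The size of the trial comes from pain alone. Section 2.7 states that "The main outcome will be the change of VAS score between the intervention group and the control group", uses "α = 0.05, statistical power of 95%, and follow-up loss of up to 20" percent, and concludes that "the sample size of this study is 45 patients per group". The limitations paragraph of the Discussion comments on the sample size but not on what it means for safety.

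**The concern.** A difference test can signal harm. It cannot establish that harm is absent, and the less information it has, the more likely it is to be non-significant. Calling the exercise a verification of safety, and naming a difference test as the only comparison, therefore pairs a strong claim with a method that cannot deliver it.

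The Introduction already describes Baduanjin as shown to be safe, while faulting earlier trials for small samples and missing safety observation. Against that background, a non-significant p-value could easily be cited as confirmation, although a clinically relevant excess of adverse events would usually have gone undetected. At stake is the safety statement that reaches clinicians and patients. The primary pain analysis is not affected.

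**Working it through.** **1. The plan's own figure.** Inputs from 2.7: "2.37 ± 1.7 in the treatment group and 3.70 ± 1.39 in the control group", alpha 0.05, power 95%, loss 20%. Sidedness is not stated; two-sided is taken here.
- Difference = 3.70 − 2.37 = 1.33. SD = √((1.7² + 1.39²)/2) = 1.553.
- n = 2 × (1.960 + 1.645)² × 1.553² / 1.33² = 35.4, rounded up to 36 per arm.
- 36 / (1 − 0.20) = 45 per arm.

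The stated 45 is reproduced by the normal approximation, so no sample-size error is alleged. The calculation contains no safety input.

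**2. What zero events would show.** This needs no assumed event rate. If none of n exposed patients has an event, the exact upper limit is 1 − 0.05^(1/n) one-sided, or 1 − 0.025^(1/n) two-sided.

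| n exposed | one-sided 95% | two-sided 95% |
|---|---|---|
| 45 | 6.4% | 7.9% |
| 36 | 8.0% | 9.7% |

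The 36 is 45 × 0.8. It is a pessimistic case, because it supposes that patients lost to follow-up contribute no safety data.

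These limits hold only with zero events. With 1 event in 45 the one-sided limit rises to 10.1%, and with 3 events to 16.3%. In the other direction, an event with a true rate of 1% would not be seen at all among 45 patients with probability 0.99^45 = 64%; at 2% the figure is 0.98^45 = 40%.

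**3. Power of the planned test.** The document gives no adverse event rate, so the rates below are assumptions, shown as a range. Power is the sum, over all pairs of counts with p ≤ 0.05 two-sided, of the product of the two binomial probabilities. Both named tests are shown, Pearson without continuity correction.

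| Control v Baduanjin | Fisher, 45/arm | Pearson, 45/arm | Fisher, 36/arm | Pearson, 36/arm |
|---|---|---|---|---|
| 5% v 10% | 6% | 16% | 3% | 13% |
| 5% v 15% | 23% | 39% | 15% | 32% |
| 5% v 20% | 48% | 63% | 34% | 53% |
| 10% v 20% | 18% | 28% | 14% | 23% |

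For scale, 80% power by the usual normal formula for two proportions needs 435 per arm for 5% v 10% and 141 per arm for 5% v 15%.

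**4. What a non-significant result would look like.** With 5 of 45 affected on Baduanjin and 2 of 45 in control, Fisher gives p = 0.43. The difference is 5/45 − 2/45 = 6.7 percentage points, with a Newcombe 95% interval from −5 to +19 points. The p-value alone hides that an excess of up to 19 points remains compatible with the data.

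The choice between the two tests can also decide the result. For 5 v 0, Fisher gives p = 0.056. Uncorrected Pearson gives χ² = 90 × (5 × 45 − 0 × 40)² / (45 × 45 × 5 × 85) = 5.29, p = 0.02.

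These calculations concern the total adverse event rate. The test of events attributed to Baduanjin adds little between arms, because controls do not practise it.

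**The case against.** The strongest case against the point has five parts.

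- **No decision rule.** A reader might infer that the trial will declare safety if the test is non-significant. The document does not support that: 2.21 says only that the rates are tested, and no section sets a pass criterion or ties a conclusion to the p-value. This objection stands in full. The point is about what the wording invites, not about a stated rule.
- **Loose wording.** The sentence is one item in a list of strengths, in an article with uneven English, and the objective in 2.1 is to evaluate. This stands in part and keeps the weight modest. The sentence is nevertheless the article's own claim for its safety component, and the closing paragraph repeats the expectation of safety evidence.
- **Descriptive safety data are already planned.** Section 2.18 provides for recording and incidence, and 2.21 reports categorical variables as frequency or percentage. This stands: the test is not the only safety output, although it is the only comparison.
- **Intervals may be in the full protocol or analysis plan.** This also stands, so their absence from the article is not itself the finding. The finding is that the claim and the method, both stated, do not match.
- **Sizing on the primary efficacy outcome is normal.** Agreed. No larger trial is called for.

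**Conclusion.** The point holds as a mismatch between claim and method. A Pearson or Fisher difference test with 45 per arm cannot verify safety. For the assumed rates of 5% v 10% to 5% v 20%, its power at 45 per arm runs from 6% to 48% (Fisher) or from 16% to 63% (uncorrected Pearson). Those figures depend on the assumed rates. The zero-event limits do not: 6.4% one-sided or 7.9% two-sided with 45 exposed patients, 8.0% or 9.7% with 36, and higher once any event occurs.

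It would go too far to say that the trial can exclude every event rate above some fixed 6% to 8%, since that bound exists only if no event is seen. Collecting and describing adverse events is sound. This is an inexpensive improvement to what the trial may conclude about safety, and it leaves the efficacy design untouched.

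**What to change.** In 2.21, make estimation the basis of the safety statement:
- per arm, the number and percentage of patients with any adverse event and with any serious adverse event, each with exact two-sided 95% limits;
- the between-arm risk difference with its 95% interval;
- a sentence saying that a non-significant test is not evidence of safety.

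In the Discussion, replace the claim to verify safety with one to describe the adverse events. Add to the limitations that, even with zero events in 45 patients, a rate of up to about 8% (two-sided 95%) could not be excluded, and that the limit is higher if any event occurs.

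The cost is a few sentences and a few lines of analysis, with no extra patients, visits or data. The downside is that the stated safety claim becomes weaker.

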### Subject withdrawal criteria

2.5

1.Violate the inclusion criteria or meet the exclusion criteria;2.Serious adverse events hindered the continuation of the trial;3.Withdraw the consent of the subject or legal representative;4.Do not receive the entire course of treatment continuously;5.The investigator or subject violates the clinical trial protocol;6.Use of drugs or treatments that may affect the results of clinical trials without the permission of the researcher;7.The researcher believes that the progress is inappropriate.

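### Withdrawal and elimination rules applied after randomisation conflict with the promised intention-to-treat analysis and are liable to bias the comparison

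*Protocol article*

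**What the plan says.** Four parts of the protocol article bear on who contributes data.

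- **Section 2.5, Subject withdrawal criteria.** The grounds for withdrawal include "Do not receive the entire course of treatment continuously", a breach of the protocol by investigator or subject, and "Use of drugs or treatments that may affect the results of clinical trials without the permission of the researcher".
- **Section 3, Discussion.** One limitation is that daily activity in the control group cannot be quantified. The text adds that, after inclusion, "we could only see those with significantly increased or decreased daily activity, and carried out elimination management".
- **Section 2.15, Participant retention and persistence.** Attendance is measured by counting training days, a missed session counts as an absence, and times can be rearranged. No withdrawal follows from an absence here.
- **Section 2.21, Statistics.** The first paragraph says: "The analysis of primary or secondary results will be established with the intent to treat principle". Values that are missing are to be multiply imputed. The later paragraph on the primary analysis says: "The statistical analysis of primary and secondary results will be based on treatment principles".

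The article does not say that a withdrawn or eliminated patient continues to be assessed, or is analysed in the assigned arm.

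**The concern.** Incomplete course, protocol breach, unpermitted treatment and changed activity all arise after randomisation. If they end a patient's participation, the later outcomes are lost for reasons tied to behaviour during the trial.

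The loss is also unlikely to be balanced. Controls have no training course to complete (sections 2.2 and 2.13), so the course rule falls in practice mainly on the Baduanjin arm. The activity rule is described for controls. Section 2.9 says that participants and physicians are not blinded, so discretionary removal can be influenced by knowledge of the arm.

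At stake is the primary endpoint, the change in VAS to week 24. Outcomes that were never collected cannot be restored by a later analysis plan.

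**Working it through.** **1. The passages side by side**

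| Event after randomisation | Consequence stated | Arm mainly affected |
|---|---|---|
| Missed training | 2.5: withdrawal if the course is not complete and continuous. 2.15: recorded as absence | Baduanjin |
| Protocol breach | 2.5: withdrawal | Either |
| Treatment without permission | 2.5: withdrawal | Either |
| Marked change in activity | Discussion: elimination | Control, as described |
| Any of these | 2.21: intention to treat, missing data imputed | Both |

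The first row contradicts itself. The last row fits the others only if withdrawn and eliminated patients stay in the analysis. Imputation could keep them there nominally, but under missing at random their later values would be inferred from patients who stayed. If imputation is done within arm, someone who stopped training is given values typical of people who continued, unless the observed data explain the difference. Removal by rule for adherence or activity makes that assumption doubtful.

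**2. The plan's own figure (section 2.7)**

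Inputs: 2.37 (SD 1.7) against 3.70 (SD 1.39), α = 0.05 (taken as two-sided, which is not stated), power 95%, loss 20%.

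- Difference: 3.70 − 2.37 = 1.33.
- Pooled SD: √[(1.7² + 1.39²)/2] = 1.553, so d = 1.33/1.553 = 0.857.
- n = 2(1.960 + 1.645)²/0.857² = 35.4, rounded up to 36 per arm.
- 36/0.8 = 45 per arm, as stated.

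If the whole 20% allowance is used, 36 per arm still give about 94.8% power by t-test. Within that allowance the issue is selection, not power.

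**3. Illustration of possible size (assumed values, completers only)**

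Suppose a share q of one arm is removed, being the lowest-ranked on a variable that correlates r with outcome. The mean of those left shifts by r·φ(z)/(1 − q), where z is the 1 − q normal quantile. Neither q nor r is in the article.

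- q = 20%: φ(z) = 0.280 and 0.280/0.8 = 0.350. The shift is 0.105 SD at r = 0.3 and 0.175 SD at r = 0.5.
- q = 30%: φ(z) = 0.348 and 0.348/0.7 = 0.497. The shift is 0.149 SD at r = 0.3 and 0.248 SD at r = 0.5.
- r = 0: the shift is zero for any q.

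With SD 1.553, in the units of section 2.7, the extremes are 0.105 × 1.553 = 0.16 and 0.248 × 1.553 = 0.39, or 12% and 29% of the planned difference of 1.33.

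A simulation with no true effect used 20,000 trials per setting, 45 per arm before removal, removal from one arm only, and a t-test on those left. The nominal 5% error rate became:

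| Removed | r = 0 | r = 0.3 | r = 0.5 |
|---|---|---|---|
| 20% | 5.0% | 7.4% | 12.4% |
| 30% | 5.3% | 9.7% | 19.5% |

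These figures do not estimate the bias left after the planned imputation and linear mixed model.

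**The case against.** The strongest reply is that section 2.5 says who is withdrawn, not whose data are discarded, and that section 2.21 governs the analysis. On that reading withdrawal may mean only stopping the training, and a withdrawn patient is imputed and analysed as randomised. The phrase about treatment principles may be a clipped translation of intention to treat. A condensed article may also leave continued follow-up to the full protocol.

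Part of this stands: the intent may be sound, and no size of bias can be read from the text. It does not remove the conflict. Elimination reads as removal from the trial, sections 2.5 and 2.15 treat the same event differently, and imputation is a weak substitute for scheduled assessments that could have been made.

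Three stronger readings are tempting but not supported.

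- **Criterion 4 would remove most of the Baduanjin arm.** With 3 × 24 = 72 sessions and independent attendance of 99% or 98%, full attendance would be 0.99^72 = 0.485 or 0.98^72 = 0.233, so 52% to 77% would be withdrawn. Those attendance rates are not in the article. Section 2.15 records absences and allows rescheduling, and section 2.7 plans for loss of up to 20%. One missed session cannot be assumed to mean withdrawal.
- **The bias must favour Baduanjin.** The activity rule covers decreases as well as increases. Losing controls who became less active could act in the opposite direction to losing those who became more active.
- **Criterion 6 flatly contradicts the conventional care allowed in section 2.10.** It applies only to treatment taken without the researcher's permission, so any conflict is partial.

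**Conclusion.** The point holds as a contradiction that affects the primary comparison. The rules in section 2.5 and the Discussion conflict with the intention-to-treat promise in section 2.21, which its own later sentence blurs, and with the handling of absences in section 2.15. Followed as written, they are liable to lose outcomes selectively and differently by arm, and imputation under missing at random may not correct this.

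Size and direction are unknown. The range of about 0.10 to 0.25 SD rests on assumed removal of 20–30% of one arm and an assumed correlation of 0.3–0.5, and describes a completers-only comparison that is not the planned analysis. If removal is unrelated to outcome, the shift is zero.

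A reader might infer that the trial is no longer a randomised comparison. The article does not support that, because it still promises intention to treat and does not say that withdrawn patients are excluded from the analysis.

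**What to change.** Reconcile sections 2.5, 2.15, 2.21 and the Discussion.

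- In section 2.5, separate stopping the training from leaving the study. State that stopping training, deviating from the protocol, taking other treatment or changing daily activity does not end follow-up.
- Unless consent is withdrawn or assessment is not possible, collect the scheduled assessments up to week 28 and analyse each patient in the arm to which they were randomised.
- Remove the elimination for changed daily activity.
- In section 2.21, replace the wording about treatment principles with the intention-to-treat principle.
- Use any completer or per-protocol set only as a sensitivity analysis.

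When training should stop for clinical reasons is left unchanged.

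The cost is a short amendment and some effort to keep in contact with patients who stop training. No visits are added, because sections 2.2 and 2.11 already schedule the assessments. The downside is that the estimate will include non-adherers and may be smaller. The change needs to be made while patients are still being followed, since missed assessments cannot be recovered.
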